### Outcomes and data collection

The primary outcome is the between-group (intervention vs control) difference in physical activity (mean MET-min/day) at 6 months, using GENEActiv accelerometers. GENEActiv is a wrist-worn accelerometer that collects continuous data and has been validated for continuous patient monitoring. Participants only wear the accelerometer for 7 days at baseline and 6 months follow-up. The accelerometer does not provide feedback to the wearer (no screen), minimising the likelihood of participants’ physical activity being impacted by accelerometer information. Accelerometers will be sent to and from participants in a reply-paid envelope, with wear instructions.^19^ Secondary outcomes, including physical activity, diet, QoL, distress, financial distress, fear of cancer recurrence, endocrine therapy medication adherence and BMI, will be collected at baseline, 6, 12, 18 and 24 months* (*if capacity/funding allow; figure 1; table 1) using accelerometers or English versions of validated or previously used self-reported questionnaires^420^,^27^ on REDCap or over the phone, in the same order every time. To reduce avoidable missing data, participants will be sent reminders (email, text message), and REDCap data quality features will be enabled. Linkage and automated extraction of de-identified clinical data from general practice, including diagnosis, medication lists and weight, will occur at baseline, 6 and 18 months.

**Table 1 T1:** Schedule of study procedures

Schedule of assessments	Study period					
	Baseline/enrolment	Allocation	Effectiveness	Maintenance		
TIME POINT	*-t_1_*	*t* _0_	*t_1_* 6 months±6 weeks	*t_2_* 12 months±6 weeks	*t_3_* 18 months±6 weeks	*t_4_* 24 months±6 weeks

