**Process evaluation**						
User feedback survey§^4^			✓			
Focus groups§			✓			
General practice staff feedback survey			✓			
General practice staff semi-structured interviews			✓			
Text message delivery and reply data^4^		✓	✓			

* European Organisation for Research and Treatment of Cancer Quality of Life Questionnaire.

† EuroQol-5 Dimension.

‡ Only for participants taking endocrine therapy medication.

§ Only for participants in the intervention group.

GPgeneral practitionerMETmetabolic equivalent

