### Sample size

Based on physical activity levels among breast cancer survivors in our pilot study,^4^ a sample size of 678 (339/group) will achieve 80% power to detect a 22.2 difference in mean physical activity MET-minutes/day between the intervention group (187.0 MET-min/day) and control group (164.8 MET-min/day) with population SD of 91.96 after accounting for 20% dropout. The significance level of the two-sided tests used was 0.05.

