### Statistical analyses

Statistical analyses will follow intention-to-treat and a prespecified Statistical Analysis Plan led by our blinded statistician, using SAS, V.9.4 and tests will be two-tailed. Categorical and continuous data will be summarised as frequencies and percentages or means and SD, respectively. For the primary outcome, a t-test will be used. As a sensitivity analysis, a linear mixed-effects regression model will be used to account for the practice clustering effect and baseline values of the primary outcome. Pre-specified sub-analysis will include major cities versus regional/rural/remote, age, gender, health literacy level, socioeconomic status and reported engagement (high vs low engagement determined by user survey). In case of non-negligible amounts of missing data (>10%), multiple imputations will be used under the missing at random assumption. For the secondary continuous and categorical outcomes, linear and logistic mixed effects regression models will be used, respectively, to account for the practice clustering effect and adjust for the outcome values at baseline.

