Adoption	Number, proportion and representativeness of participating practices, based on the practice postcode and size (number of patients per year); and reasons for non-adoption (declining to deliver the study)
Implementation	
Patient-reported experience measures (acceptability, utility, engagement)	User feedback survey (intervention group only): 17 questions, 15 multiple-choice with 5-point Likert scale (1=strongly disagree to 5=strongly agree), yes/no or select all that apply and two free-text responsesFocus groups with a subset of intervention participants (approximately 24 participants)Text message delivery data: number, and content of text message replies, including text, emojis (a small digital image or icon used to express an idea or emotion) or ‘reactions’, which occur when a participant clicks a text message and clicks ‘like’, ‘love’ or ‘emphasise’
Intervention Fidelity	Text message delivery data: number of text messages successfully delivered or unsuccessfully delivered (bounced). Percentage of opt-outs (n opt-outs/n baseline × 100), based on ‘STOP’ or opt-out request text message replies from intervention participantsAdaptations to the intervention or implementation processes: Log of any changes made during the study period
Feasibility	Setting-level direct intervention costs, including delivering the text messages, monthly fees for the automated text message delivery software, including general practice computer software.Individual-levelFit-for-purpose feedback survey for general practice staff members (GPs, allied health, practice managers or receptionists) to identify barriers/enablers to implementation, estimated general practice staff time and costs to identify eligible patients and send text message invitation. Semi-structured interviews with staff members (GPs, allied health, practice managers, receptionists)
Maintenance	Between-group differences in secondary outcomes (effect size, 95% CI) at 12, 18 and 24 months*

* if capacity/funding allow.

GPgeneral practitionerREDCapResearch Electronic Data Capture

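### Engagement is listed with the pre-specified sub-analyses but is measured only in the intervention arm at 6 months, so it cannot show a treatment effect by engagement level

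*Protocol article*

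**What the plan says.** In the protocol article, the Statistical analyses section opens with the principle that "Statistical analyses will follow intention-to-treat". After the primary t-test and its mixed-model sensitivity analysis it adds: "Pre-specified sub-analysis will include major cities versus regional/rural/remote, age, gender, health literacy level, socioeconomic status", and closes the same list with "reported engagement (high vs low engagement determined by user survey"). It does not say which contrast the engagement item means, and it does not mark that item off from the others.

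Two other places fix who answers the survey and when. Table 1 ticks the user feedback survey in the 6-month column only, with a footnote: "Only for participants in the intervention group". Table 2 (Process evaluation, Implementation) repeats it: "User feedback survey (intervention group only"), and files engagement with acceptability and utility as patient-reported experience.

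The 6-month visit is also where the primary outcome is taken: "The primary outcome is the between-group (intervention vs control) difference in physical activity (mean MET-min/day) at 6 months".

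**The concern.** A sub-analysis by age or remoteness compares intervention with control inside each level, so randomisation still protects the comparison. That requires every participant in both arms to have a value that treatment could not have altered. Engagement fails on both counts: controls have no value, and for intervention participants it is recorded after six months of messages, at the same visit as the outcome.

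People who report high engagement may be those who were already more active or more motivated. People who became more active for any reason may look back on the messages more favourably. Either route produces an association between engagement and activity even if the programme has no effect. Because the item carries pre-specified status and sits among valid subgroups, such an association could be read as evidence that the programme works in those who use it. This trial is meant to inform scale-up, so that reading matters.

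**Working it through.** **1. The article's own figure.** The Sample size section states that "a sample size of 678 (339/group) will achieve 80% power" for a difference of 22.2 (187.0 − 164.8), SD 91.96, two-sided 0.05 and 20% dropout. The t-based calculation gives 270.3, rounded up to 271 per group; 271 / 0.8 = 338.75, so 339 per group and 678 in total. This reproduces exactly and is not in dispute. The 271 per arm is used below as the analysed number.

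**2. What can be estimated.** Let T be arm and E be engagement (1 high, 0 low). A subgroup analysis needs the model

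mean activity = a + b·T + c·E + d·(T×E),

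where d is the treatment-by-engagement effect. E is undefined for every control (0 of 339 can be classified). If controls are coded E = 0, the columns E and T×E become identical and only c + d can be estimated. That sum is the high-minus-low difference within the intervention arm. It mixes any effect modification with whatever already separates engagers from non-engagers. Replies, reactions and opt-outs, the other engagement data in Table 2, also arise only from receiving the programme, so they do not supply a control value.

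**3. How large a spurious difference could be.** The article gives no correlation between engagement and activity, so the following are assumptions: zero true effect, SD 91.96 (Sample size section), engagement split at the median, jointly normal engagement and activity with correlation ρ in the intervention arm, every analysed participant answers the survey, and no baseline adjustment.

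The mean of a standard normal variable above its median is √(2/π) = 0.798. Hence:

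- high engagers minus all controls = ρ × 91.96 × 0.798 = ρ × 73.4
- high minus low within the intervention arm = twice that = ρ × 146.7

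| ρ | High vs controls (MET-min/day) | High vs low within arm (MET-min/day) |
|---|---|---|
| 0.1 | 7.3 | 14.7 |
| 0.2 | 14.7 | 29.3 |
| 0.3 | 22.0 | 44.0 |

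The within-arm difference equals the planned 22.2 at ρ = 22.2 / 146.7 = 0.15. The comparison with controls reaches it at ρ = 22.2 / 73.4 = 0.30.

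**4. How often it would be significant.** In 4,000 simulated trials per value of ρ, with 271 analysed per arm and no treatment effect, the mean differences agreed with the formula (7.3, 14.8 and 21.9 against controls; 14.7, 29.4 and 43.9 within the arm). The share with p < 0.05 was:

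| ρ | High vs controls | High vs low within arm |
|---|---|---|
| 0 | 5% | 5% |
| 0.1 | 12% | 26% |
| 0.2 | 33% | 76% |
| 0.3 | 62% | 98% |

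**5. Effect of baseline adjustment.** Accelerometer activity is measured at baseline. If the model adjusts for it, the relevant ρ is the correlation that remains given baseline activity. That is expected to be smaller, so the figures in step 3 shrink. Motivation not captured by baseline activity, and reverse causation at 6 months, remain.

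**The case against.** The article says sub-analysis, not treatment-effect subgroup or interaction, and names no comparison of engagers with controls. A high-versus-low comparison within the intervention arm is feasible, and Table 2 treats engagement as a patient-experience measure, which fits a descriptive purpose. The contrast, the adjustment and an exploratory label are details that may sit in the statistical analysis plan, which was not available here. The correlations and the median split come from no document. The unadjusted figures are one scenario, since the article adjusts for baseline in its primary sensitivity analysis and its secondary-outcome models.

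Most of this stands, and it limits the point. A reader might infer that the result will certainly be confounded, or that the trial plans to claim the programme works in those who engage. The documents support neither: no such claim is stated, and the size of any bias depends on a correlation they do not give.

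What does not fall away is the listing itself. Engagement is placed with factors defined in both arms, without distinction and under an intention-to-treat heading. An analysis plan can supply a cut-off or a label, but it cannot supply control values from a survey controls never receive.

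**Conclusion.** The point holds in a limited form. As listed, engagement cannot serve as a subgroup for the treatment effect, and this follows from Tables 1 and 2 without any assumption. Any contrast that can be computed is non-randomised and restricted to survey responders. The range of roughly 7 to 22 MET-min/day against controls, or 15 to 44 within the arm, is illustrative. It rests on assumed correlations of 0.1 to 0.3, a median split, a null effect and no baseline adjustment. It shows only that modest correlations could yield differences of the same order as the planned 22.2.

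It might be tempting to call this a must-fix. That is not supported: the primary t-test, the sample size, the secondary-outcome models and the other sub-analyses are untouched. It is a should-fix.

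**What to change.** Take reported engagement out of the list of pre-specified sub-analyses. Report it in the process evaluation as an exploratory, non-randomised association within the intervention arm, adjusted for baseline accelerometer activity. Give the number of survey responders, and state that no treatment effect in engaged participants will be claimed.

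A complier average causal effect, with randomisation as the instrument, is optional. It should be added only with an exposure definition for which the exclusion restriction is plausible. Defining exposure as not opting out would be weak: it measures persistence with delivery rather than reported engagement, and a late opt-out has already received many of the 104 messages yet would count as unexposed. Such an estimate would also be less precise than the intention-to-treat one.

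The cost is a sentence in the protocol and the matching wording in the statistical analysis plan, before unblinding. No new data are needed. What is given up is the pre-specified subgroup status of the engagement result.

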**Trial registration number:**

Australia and New Zealand Clinical Trial Registry (ACTRN12624000591550, 09/05/2024; U1111-1307-3454).

STRENGTHS AND LIMITATIONS OF THIS STUDYThis is a high-quality evaluation of the short-term (6 months) and long-term (12, 18, 24 months) effectiveness of low-cost, scalable, co-designed text message intervention sent from general practice to manage survivors’ risk factors compared with usual care.Evaluating barriers and enablers to implementation into general practices using the Reach Effectiveness Adoption Implementation and Maintenance framework will provide important insights into practice staff’s and patients’ perspectives.Recruiting from general practices across Australia will improve the likelihood of a representative sample of participants.Enrolment and electronic consent via the Internet can enable rapid recruitment of participants. However, it may also cause limitations for individuals with lower digital health literacy.Measuring physical activity (primary outcome) with wrist-worn accelerometers will provide objective data with high sensitivity. However, non-adherence may lead to missing data.

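### Multiple imputation is triggered only above 10% missing although 20% dropout is planned; one baseline-adjusted primary estimator should be fixed whatever the amount missing

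*Protocol article*

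**What the plan says.** The Statistical analyses section of the protocol article sets the primary method in one sentence: "For the primary outcome, a t-test will be used". It then adds, with the closing noun omitted here: "As a sensitivity analysis, a linear mixed-effects regression model will be used to account for the practice clustering effect and baseline values of the primary". On missing data it gives one rule: "In case of non-negligible amounts of missing data (>10%), multiple imputations will be used under the missing at random assumption". The same section defers to a separate document: "Statistical analyses will follow intention-to-treat and a prespecified Statistical Analysis Plan led by our blinded statistician". That plan is not shown.

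The Sample size section states that "a sample size of 678 (339/group) will achieve 80% power", for a difference of 22.2 MET-min/day, "with population SD of 91.96 after accounting for 20% dropout". The strengths and limitations box says of the accelerometer: "However, non-adherence may lead to missing data". Under Outcomes and data collection, and in Table 1, the accelerometer is worn for 7 days at baseline and again at 6 months, so a baseline value of the primary outcome is collected.

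**The concern.** The rule uses the proportion missing to decide whether missing data need handling. That proportion does not measure bias. A t-test on returned devices is distorted when the people who drop out differ in activity and do so differently in the two arms. A small loss that is unbalanced in this way can bias the comparison, while a larger loss of the same kind in both arms may not.

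The article gives some reason to think that the arms could differ. Participants are told their allocation (Randomisation, blinding and concealment). Only the intervention arm receives several messages a week, with a monitored reply channel that also takes withdrawal requests (Group allocation).

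Below the trigger, the main result leaves out the one measured variable most likely to explain such loss, the baseline accelerometer value. Above it, the rule treats as a contingency a level of loss that the trial's own sample size takes as its planning case.

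**Working it through.** **1. The plan's own figure.** Inputs from the Sample size section: difference 22.2, SD 91.96, two-sided alpha 0.05, power 80%, dropout 20%. The normal formula gives 2 × (1.960 + 0.842)² × 91.96² / 22.2² = 269.4, so 270 per group. The exact noncentral-t calculation gives 271 per group (power 80.1%). Then 271 / 0.80 = 338.75, so 339 per group and 678 in total. The stated N is reproduced, and the 20% is built into it.

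**2. How often the trigger fires.** Read the 10% as overall missingness in the primary outcome (an assumption). The trigger then needs at least 68 of 678 missing, since 0.10 × 678 = 67.8. Binomial probabilities:

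| True proportion missing | P(trigger fires) |
|---|---|
| 8% | 0.03 |
| 10% | 0.51 |
| 12% | 0.95 |
| 15% | >0.999 |
| 20% (planned) | >0.999 |

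**3. Bias of the complete-case t-test below the trigger.** Let x be standardised baseline activity, r its correlation with the 6-month value, and let the log-odds of being missing fall by 0.8 per SD of x. Slope and r are assumptions; the article gives neither. Then

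bias = 91.96 × r × (mean of x among observed intervention participants − mean of x among observed controls),

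with intercepts set to give the stated loss. Overall loss is 9% in every row, so imputation is not triggered.

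| Loss, intervention / control | Slope, intervention / control | Mean of x among observed | Bias, r = 0.5 to 0.7 | Share of 22.2 |
|---|---|---|---|---|
| 9% / 9% | 0.8 / 0 | 0.068 / 0 | +3.1 to +4.4 | 14 to 20% |
| 12% / 6% | 0.8 / 0 | 0.0895 / 0 | +4.1 to +5.8 | 19 to 26% |
| 12% / 6% | 0.8 / 0.8 | 0.0895 / 0.046 | +2.0 to +2.8 | 9 to 13% |
| 9% / 9% | 0.4 / 0 | 0.0355 / 0 | +1.6 to +2.3 | 7 to 10% |
| 9% / 9% | 0.8 / 0.8 | 0.068 / 0.068 | 0 | 0 |

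Example, second row at r = 0.7: 91.96 × 0.7 × 0.0895 = 5.8.

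At 9% loss about 308 per group remain, and the standard error is 91.96 × √(2/308) = 7.4. Biases of 3.1 to 5.8 are therefore about 0.4 to 0.8 standard errors, and they would raise a nominal 5% two-sided type I error to about 7 to 12%. In these scenarios loss depends only on arm and measured baseline, so a model that adjusts for baseline removes the bias.

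**4. Precision.** With 271 per arm the unadjusted standard error is 91.96 × √(2/271) = 7.90, for 80% power. Adjusting for baseline at an assumed r = 0.5 multiplies it by √(1 − 0.25), giving 6.84 and power of about 90%.

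**The case against.** The strongest reply is that the rule is prespecified and depends on the amount missing, not on the treatment effect. At 15 to 20% loss it is practically certain to select imputation; the branch is in real doubt only at about 8 to 12%. In a simulation of the rule with data missing completely at random (assumed r = 0.6), type I error was 0.050 at 10% missing and 0.047 at 20%. This stands: a reader might infer that the trial's conclusion hangs on a data-driven switch, and at the planned loss it does not. The simulation does not answer the bias point, because the complete-case t-test is unbiased by construction when data are missing completely at random.

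A 20% recruitment allowance and a 10% analysis trigger do not contradict each other either. Nor does the article say outright that imputation replaces the t-test, or whether the 10% is overall or per arm. Replacement of the complete-case result is the natural reading, not explicit text.

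The bias figures rest on an assumed slope and, for the larger ones, on selection in one arm only. No document supports either. With equal slope and equal loss the bias is zero, so it does not follow that the complete-case result is biased whenever loss is 10% or less.

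The baseline-adjusted model is already planned, with no missingness condition attached, so a reader of the full results would see it. But it would appear as a sensitivity analysis beside a less robust headline.

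A reader might also infer that the trial has no protection against non-wear related to unobserved inactivity. The article does not support that. Stating missing at random for the imputation does not exclude a not-at-random analysis, and such detail, like the choice of auxiliary variables, is commonly left to the SAP that the article cites.

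**Conclusion.** The point holds as a weakness in a rule that the article states. The trigger is a poor criterion. At or below 10% missing it leaves as the headline an unadjusted complete-case comparison that ignores a collected baseline value. Under the assumptions above, this could carry a bias of about +2 to +6 MET-min/day where loss related to baseline activity differs by arm in slope or rate (about +1.6 to +2.3 at half the one-sided slope), and none where both are equal. At the planned 20% loss the complete-case t-test is not the analysis that the trial should expect to report. The figures show what is possible; they do not predict what will happen. The point does not extend to inflated type I error from the switch itself, or to a missing not-at-random analysis.

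**What to change.** Delete the 10% trigger and name one primary estimator for use whatever the amount missing. The natural choice is the linear mixed model already planned as a sensitivity analysis, with a practice effect and baseline MET-min/day, together with one fixed missing-data method. Keep the unadjusted t-test as a supporting analysis. Make the change before unblinding.

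The cost is SAP wording and minor programming. No new data are needed and N stays 678.

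As a recommendation only, confirm that the SAP contains a delta-adjusted analysis for values missing not at random. For scale: at 20% missing, an estimated difference of 22.2 would lose significance if missing intervention-arm values were lower than imputed by about (22.2 − 15.5) / 0.20 ≈ 33 MET-min/day (0.36 SD), with no shift in controls. Here 15.5 is the critical difference on the complete-case standard error of 7.90.

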### Process evaluation

A mixed-methods approach will be used following the enhanced RE-AIM framework (table 2).^17^ Setting-level and patient-level data sources will include participant demographics, text message delivery data, and patient and general practice staff feedback surveys. In addition, focus groups will be conducted with intervention participants and semi-structured interviews will be conducted with general practice staff, including GPs, practice managers, practice nurses and receptionists. The sample size will be based on thematic saturation. However, it is estimated that approximately 24 intervention participants and 24 practice staff members will be required. Maximum variation sampling will be used based on participants’ postcode, age and ancestry to ensure a range of views are obtained. The focus groups and interviews will be conducted via videoconference or phone by a trained interviewer using a discussion guide and will be audio recorded and transcribed verbatim. Transcripts will be de-identified and provided to participants for review on request. Quantitative data will be summarised using frequencies and percentages or means and SD. Qualitative data will be parallel coded by two researchers with qualitative research experience in NVivo (QSR International) using the enhanced RE-AIM framework.^17^ Codes will be compared for inter-coder reliability and disagreements will be discussed with a third independent researcher until an agreement is reached. Direct quotations will be used as exemplars of overarching themes and subthemes.

**Table 2 T2:** Process evaluation using the enhanced RE-AIM framework

Framework category	Measurements
Reach	Proportion of eligible patients enrolled (n enrolled/n eligible × 100)
Representativeness	Demographics: age (years), ancestry, country of birth, gender identity, work status, treatment type, time since completing active treatment. Postcode will be used to determine participants’ Index of Relative Socioeconomic Advantage and Disadvantage (quintiles from one most- to five least disadvantaged area) and Australian Statistical Geography Standard of Remoteness Areas (categorise: Major City, Inner Regional, Outer Regional, Remote, Very Remote)
Effectiveness	Effect size of primary and secondary outcome (95% CI)
Adoption	Number, proportion and representativeness of participating practices, based on the practice postcode and size (number of patients per year); and reasons for non-adoption (declining to deliver the study)
Implementation	
Patient-reported experience measures (acceptability, utility, engagement)	User feedback survey (intervention group only): 17 questions, 15 multiple-choice with 5-point Likert scale (1=strongly disagree to 5=strongly agree), yes/no or select all that apply and two free-text responsesFocus groups with a subset of intervention participants (approximately 24 participants)Text message delivery data: number, and content of text message replies, including text, emojis (a small digital image or icon used to express an idea or emotion) or ‘reactions’, which occur when a participant clicks a text message and clicks ‘like’, ‘love’ or ‘emphasise’
Intervention Fidelity	Text message delivery data: number of text messages successfully delivered or unsuccessfully delivered (bounced). Percentage of opt-outs (n opt-outs/n baseline × 100), based on ‘STOP’ or opt-out request text message replies from intervention participantsAdaptations to the intervention or implementation processes: Log of any changes made during the study period
Feasibility	Setting-level direct intervention costs, including delivering the text messages, monthly fees for the automated text message delivery software, including general practice computer software.Individual-levelFit-for-purpose feedback survey for general practice staff members (GPs, allied health, practice managers or receptionists) to identify barriers/enablers to implementation, estimated general practice staff time and costs to identify eligible patients and send text message invitation. Semi-structured interviews with staff members (GPs, allied health, practice managers, receptionists)
Maintenance	Between-group differences in secondary outcomes (effect size, 95% CI) at 12, 18 and 24 months*

* if capacity/funding allow.

GPgeneral practitionerREDCapResearch Electronic Data Capture

